### Data Collection

Data collection will include both questionnaire surveys and anthropometric measurements, carried out at the beginning and end of the study. The 2024 Student Health Status and Influencing Factors Survey, integrated with the provincial Surveillance for Common Disease and Health Risk Factors Among Students project, will be administered before the study begins and after it concludes. Both students and their parents will complete the survey, which is provided by national authorities and includes versions for primary and secondary school students. The survey covers general demographic characteristics, dietary habits, physical activity, smoking and drinking behaviors, use of eyes outside of school, electronic screen use, outdoor activities, and sleep habits. Additionally, parental KAP questionnaires for the intervention group will be collected at baseline and 3, 6, 9, and 12 months, while those for the control group will be obtained at baseline and after 12 months. Nutritional status monitoring will include measurements of height, weight, and waist circumference following standardized procedures with light clothing and without shoes. BMI will be calculated as weight in kilograms divided by height in meters squared (kg/m^2^). Waist circumference will be measured horizontally at the midpoint between the last rib and the top of the iliac crest. General obesity will be determined by sex- and age-specific BMI cutoff values according to the Screening Standard for Overweight and Obesity Among School-Age Children and Adolescents (WS/T 586-2018). Central obesity will be based on the 90th percentile of waist circumference by sex and age according to the High Waist Circumference Screening Threshold for Children and Adolescents Aged 7-18 Years (WS/T 611-2018). Data collected from paper-based questionnaires will be independently double-entered by 2 trained university students and subsequently entered into an electronic database.

### Statistical Analysis

The collected data will be analyzed to evaluate the effectiveness of the enhanced family-based educational interventions. Descriptive statistics will summarize baseline characteristics of the intervention and control groups, with means (SDs) or medians (IQRs) for continuous variables and frequencies (percentages) for categorical variables. Comparisons between groups will be made using independent sample 2-tailed *t* tests or Wilcoxon rank-sum tests for continuous variables and chi-square tests or Fisher exact tests for categorical variables. Multivariable regression analyses will adjust for potential confounders and assess the intervention’s independent effects on primary and secondary outcomes, including changes in BMI, zBMI, zWHtR, and zWC over 12 months. Parental KAP scores will be the sum of scores in each questionnaire entry, which will be scored on a scale of 1 to 4 depending on the option. KAP scores from the intervention group will be assessed every 3 months, and the difference between KAP scores at the start and the end of the study will be used to evaluate changes in health literacy.

To address the handling of missing data in our study, we will use a combination of intention-to-treat, per-protocol, and complete case analyses. The intention-to-treat analysis will include all participants as randomized to account for nonadherence and dropouts, thereby preserving the randomization’s integrity. The per-protocol analysis will focus on participants who complete the intervention according to the study protocol, offering insights into the efficacy under ideal adherence. Additionally, we will conduct a complete case analysis, which considers only those participants with complete data on all variables of interest. This approach will allow us to maintain the rigor of our statistical evaluation while acknowledging the limitations associated with missing data.

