### Study Outcomes

Primary outcomes are the changes in BMI and standardized BMI (zBMI) over a 12-month period. These outcomes will provide a direct measure of the intervention’s effectiveness in reducing overweight and obesity among the participants. The change in BMI will be assessed from baseline to the end of the study, while the change in zBMI will account for age and sex differences, offering a more nuanced understanding of the weight status changes in the school-aged children and adolescents.

Secondary outcomes include the incidence and recovery rates of both general and central obesity; changes in standardized waist-to-height ratio (zWHtR) and standardized waist circumference (zWC); and changes in parental knowledge, attitude, and practice (KAP) scores (Multimedia Appendix 3) [33]. Specifically, the incidence of general obesity will be determined by newly diagnosed students with obesity at the end of the study among participants who are not obese at baseline, and the recovery rate will be calculated based on the number of students who transition from obesity to nonobesity status. Similarly, the incidence and recovery rates of central obesity will be assessed. Additional secondary outcomes involve changes in zWHtR and zWC over 12 months. The staff who measure the children’s weight and height will be blinded to the school allocation. Furthermore, KAP scores will be assessed at the start of the intervention and at 3, 6, 9, and 12 months after the intervention to gauge improvements in health literacy regarding childhood and adolescent overweight and obesity. These comprehensive outcomes will help elucidate the effectiveness of the enhanced family-based educational interventions and their impact on health behaviors and literacy.

Process evaluation will be used to evaluate the feasibility and acceptability of the trial by assessing parental compliance. Specifically, parent questionnaires (Multimedia Appendix 4) are administered at 3, 6, 9, and 12 months after the intervention to evaluate adherence to dietary and physical activity recommendations.

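### The analysis sentence for parental KAP names only the intervention group and no control comparison, and the five-versus-two KAP schedule leaves any between-arm contrast open to an unacknowledged retest effect

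*Protocol article*

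**What the plan says.** In the Protocol article, Study Outcomes lists "changes in parental knowledge, attitude, and practice (KAP) scores" among the secondary outcomes and gives the schedule without naming an arm: "KAP scores will be assessed at the start of the intervention and at 3, 6, 9, and 12 months after the intervention".

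Data Collection separates the arms. One clause says that "parental KAP questionnaires for the intervention group will be collected at baseline and 3, 6, 9, and 12 months". The next clause sets only two rounds for the other arm: "while those for the control group will be obtained at baseline and after 12 months". Table 2 agrees. The December 2024 and December 2025 KAP rounds are marked for all participants, and those of March, June and September 2025 for the intervention group only.

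Statistical Analysis has three sentences that bear on KAP:

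- A general one on group comparisons, placed directly after the description of baseline characteristics: "Comparisons between groups will be made using independent sample 2-tailed *t* tests or Wilcoxon rank-sum tests for continuous variables".
- A general one on multivariable regression, which is to "assess the intervention’s independent effects on primary and secondary outcomes, including changes in BMI, zBMI, zWHtR, and zWC over 12 months".
- The only one specific to KAP analysis: "KAP scores from the intervention group will be assessed every 3 months, and the difference between KAP scores at the start and the end". That difference is to serve as the measure of change in health literacy.

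**The concern.** The KAP sentence opens with the intervention group, moves to a start-to-end difference and stops. It mentions neither the control arm nor a contrast. KAP is also not among the outcomes named in the regression sentence. Hypothesized Findings follows the same pattern: the anthropometric hypotheses are worded against control, whereas the one on health literacy has no comparator.

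A before-after gain in one arm contains whatever would have happened anyway over a year, together with any effect of answering the same form repeatedly. Raising parental awareness is the mechanism by which the trial expects to work, so a claim about health literacy will be read as evidence for that mechanism and should rest on the randomised comparison.

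The unequal schedule is a second, separate problem. It persists even when the arms are compared, because intervention parents meet the KAP form three more times than control parents before the final assessment.

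**Working it through.** The article gives no figure for KAP (no SD, expected change or retest effect), so there is none to reproduce. The check is a count of rounds followed by an illustration on stated assumptions.

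**1. KAP rounds, from Data Collection and Table 2**

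- Intervention: baseline, 3, 6, 9 and 12 months = 5 rounds, so 5 − 1 = 4 completions before month 12.
- Control: baseline and 12 months = 2 rounds, so 2 − 1 = 1 completion before month 12.
- Excess in the intervention arm: 4 − 1 = 3.

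A separate parent compliance questionnaire comes on top. Its forms "are administered at 3, 6, 9, and 12 months after the intervention to evaluate adherence to dietary and physical activity recommendations", and Table 2 marks them for the intervention group only (4 versus 0). Counting both instruments gives 5 + 4 = 9 forms versus 2.

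**2. Time points shared by both arms**

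Baseline and month 12. A randomised comparison of KAP is therefore possible with data already planned.

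**3. What each analysis would estimate**

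Let t be the true effect, s a time trend common to both arms, and g the gain per earlier completion, taken as additive. All are in SD units, and g and s are assumptions.

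- Change within intervention = t + s + 4g
- Change within control = s + g
- Between-arm difference = (t + s + 4g) − (s + g) = t + 3g

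With t = 0:

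| g (assumed) | Within intervention, s = 0 | Within intervention, s = 0.10 | Between-arm difference, either s |
|---|---|---|---|
| 0 | 0 | 0.10 | 0 |
| 0.02 | 0.08 | 0.18 | 0.06 |
| 0.05 | 0.20 | 0.30 | 0.15 |
| 0.10 | 0.40 | 0.50 | 0.30 |

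The common trend goes entirely into the within-arm change and cancels in the contrast. The retest term shrinks from 4g to 3g but does not cancel. Under the same additive assumptions, adjusting for baseline leaves the 3g in place, since randomised arms have the same expected baseline.

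**4. Does the text fix a within-arm analysis?**

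The regression sentence covers secondary outcomes, and KAP change is one. The outcomes it then names are introduced as examples: the incidence and recovery rates of general and central obesity are also secondary and also missing from it. KAP's absence from the list is therefore weak evidence that it is excluded. The text permits both readings.

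**The case against.** The strongest reply is that a between-arm analysis is already covered. The regression sentence extends to secondary outcomes. Only the first clause of the KAP sentence is limited to the intervention group; the second names no arm and uses exactly the two time points that both arms share. Collecting control KAP at those points would make little sense unless the arms were to be compared. This stands. A reader might infer that the plan replaces the randomised contrast with a within-arm change and so credits all background and retest change to the intervention. The documents do not support that; they leave the comparison unstated.

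A reader might also infer that part of any KAP gain must be familiarity with the form. That is not supported either: nothing in the article shows a retest effect for rounds three months apart, and it may be zero.

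On the schedule, Study Outcomes can be read as a general statement that Data Collection and Table 2 then make specific. The latter two agree, so the intended schedule is not in real doubt, and only the wording of Study Outcomes needs aligning.

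Finally, model terms for a secondary outcome are often left to a statistical analysis plan, which is not at hand. That is fair as to detail. It does not answer the point, because the article does state a KAP analysis and words it so that the comparator is unclear.

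**Conclusion.** The concern holds as one of ambiguity and non-disclosure. The KAP-specific sentence describes a start-to-end difference, names only the intervention group and leaves the comparison with control unstated. An analyst could follow it literally and report an uncontrolled gain as an effect, although control values at baseline and 12 months will exist.

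The 5-versus-2 count is firm. Its consequence is not quantifiable from the documents. For g between 0 and 0.10 SD and no true effect, the between-arm contrast would show 0 to 0.30 SD; the within-arm change would show 0 to 0.40 SD before any time trend. These ranges rest on the assumed g and on additivity. Strengths and Limitations mentions monitoring of parental health literacy but not the unequal rounds.

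The point concerns a secondary outcome only. The BMI and zBMI analyses do not depend on it.

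**What to change.** 1. In Statistical Analysis, state that the KAP secondary outcome is the between-arm difference in 12-month KAP score, adjusted for baseline KAP and the randomisation strata and allowing for clustering by school, using only the two time points common to both arms.
2. Report the month 3, 6 and 9 scores descriptively, as process data from the intervention arm.
3. Reword Study Outcomes so that its KAP schedule matches Data Collection and Table 2.
4. Add to the limitations that intervention parents complete the KAP form five times and control parents twice, so the contrast may include a retest effect of unknown size, possibly zero. Disclose this as a limitation; do not describe the extra rounds as part of the intervention, because Table 1 defines the components without any KAP questionnaire.

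The cost is wording and one prespecified model. No new data are needed, and because analysis is to begin only after the 12-month assessments, the change can be recorded before any KAP comparison is run. The first step removes the ambiguity and any common time trend. It does not remove unequal retesting, which is why the fourth is needed as well.

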### Ethical Considerations

This study protocol was reviewed and approved by the institutional review board of the School of Public Health, Sun Yat-sen University (approval number 2024-160). Informed consent will be obtained from all participants and their parents or guardians prior to enrollment in the study. All procedures will be conducted in accordance with the ethical standards of the responsible committee and the World Medical Association Declaration of Helsinki. Participant confidentiality will be ensured by assigning unique study IDs, and privacy will be strictly protected. Any participant who experiences harm related to trial participation will receive appropriate medical care and compensation.

## Results

This trial was funded in January 2024. The study recruitment is scheduled to be completed before December 2024. The intervention will be integrated with the 2024 Surveillance for Common Disease and Health Risk Factors Among Students in Guangdong Province initiative. Baseline data will be collected during the 2024 and 2025 fall semester. Within 1 month, the local Center for Disease Control and Prevention will provide the intervention group with health reports and educational materials (including an enhanced health education booklet, a family weight management action guideline, and an advocacy letter). Educational materials will also be sent to the intervention group at 3, 6, and 9 months after the first intervention. Health reports are provided at the first intervention. The control group will continue with regular school-based prevention measures. The total intervention duration lasts 9 months, with 4 rounds of intervention. Table 2 shows the timeline of the study implementation. Data collection is scheduled to conclude in December 2025. Data analysis will begin after completion of the 12-month assessments. At the time of manuscript submission, baseline data collection was complete, with 20 schools enrolled in each of the intervention and control groups. Descriptive and analytic results are expected to be published in 2026.

**Table 2. T2:** Timeline of the study implementation.

Task	November-December 2024		January-December 2025											
	November	December	January	February	March	April	May	June	July	August	September	October	November	December
Ethics approval and clinical trial registration	✓^a^													
Sampled school and class determination	✓^a^													
Staff training	✓^a^													
Student survey questionnaire distribution		✓^b^												✓^b^
Parental KAP^c^ questionnaire distribution		✓^b^			✓^d^			✓^d^			✓^d^			✓^b^
Student health check-up		✓^b^												✓^b^
Health report distribution		✓^d^												
Enhanced health education booklet distribution		✓^d^			✓^d^			✓^d^			✓^d^			
Advocacy letter distribution		✓^d^			✓^d^			✓^d^			✓^d^			
Family weight management action guideline distribution		✓^d^			✓^d^			✓^d^			✓^d^			
Parental compliance questionnaire distribution					✓^d^			✓^d^			✓^d^			✓^d^

a Preliminary preparation work.

b Tasks for all participants.

c KAP: knowledge, attitude, and practice.

d Tasks only for the intervention group.

## Discussion

### Hypothesized Findings

The enhanced family-based educational intervention described here is anticipated to be effective for obesity control, reducing the prevalence of overweight and obesity among children and adolescents in Guangdong Province. We hypothesize that, compared with the control group, the intervention group will show significantly more favorable changes in BMI, zBMI, zWHtR, and zWC over the 12-month period. We also anticipate a significantly lower incidence of general obesity and a higher recovery rate in the intervention group. Furthermore, the intervention is expected to improve parental health literacy. This study integrates surveillance feedback with an enhanced family-based educational intervention, aiming to generate critical evidence to inform obesity prevention and control policies in China.

### Comparison to Prior Work

Previous intervention studies with family involvement have been predominantly conducted in single, high-income cities [28-32], limiting the generalizability of their findings to populations with different economic levels in China. Furthermore, these studies overlooked standardized family guidelines and the timely feedback of surveillance results to parents [34], neglecting elements essential for sustained engagement. To address these gaps, this study uses a multicity cluster RCT design across cities of varying economic levels. Additionally, we will provide structured educational materials, including the actionable “Three 1/2s” initiatives and child health reports for parents, aiming to facilitate practical implementation and enhance family engagement.

### Strengths and Limitations

This study has some strengths, including randomly selecting 4 cities from 2 economic strata to enhance representativeness. Additionally, schools will serve as the unit of intervention, rather than individuals, to minimize contamination between groups and improve implementation feasibility. Several limitations should be acknowledged. First, although a relatively short follow-up period may limit the detection of significant intervention effects on the control of overweight or obesity, we implemented 4 rounds of enhanced intervention, with continuous process evaluations and monitoring of parental health literacy. Second, although the study protocol does not include tailored, culturally adaptive materials, analyzing the data for differential effects across socioeconomic subgroups may provide insights to inform future refinements of intervention strategies. Finally, the anthropometric measurements will be performed only at baseline and at the end of the study based on the provincial Surveillance for Common Disease and Health Risk Factors Among Students project. The 2-point measurements restrict our ability to capture the dynamic trajectories of nutritional status during the study. Future studies incorporating more detailed and frequent measurements are warranted to better characterize the temporal trajectories of the intervention effects.

### Future Directions

This study aims to assess the effectiveness of a cost-effective family-based educational intervention to address childhood obesity in China. If proven effective, this framework could provide a scalable solution for nationwide implementation. Future research may explore tailored strategies across diverse socioeconomic and urban-rural contexts to enhance intervention effectiveness. In addition, identifying the optimal frequency of parental reporting would be valuable for maximizing long-term adherence.

### Dissemination Plan

Study results will be published in peer-reviewed journals and presented at conferences and relevant stakeholder engagement activities. No information that can identify participants will be included in any publication. Participants who explicitly express a wish to be informed about the study outcome will be contacted and provided with an article or poster containing a lay summary of findings.

### Conclusions

This cluster RCT will evaluate the effectiveness of an enhanced family-based educational intervention in children and adolescents with overweight or obesity. By integrating parental reporting into the existing provincial health surveillance system, the study aims to bridge the critical gap between school-based screening and family-based management, addressing widespread underrecognition of childhood obesity. The findings will provide evidence on the efficacy and feasibility of this scalable, family-based model. If proven effective, this approach could be incorporated into national surveillance programs, offering a sustainable public health strategy to curb the growing obesity epidemic.
